### 2.8. Statistical Analysis

To assess the effectiveness of randomization, baseline (pre-test) values will be compared between the EG and the CG for potential clinically important differences using independent samples *t*-tests for continuous variables and chi-square tests for categorical variables. Effect sizes will be calculated to quantify the magnitude of any differences observed. The difference between groups in the change (pre, post, and 8-week follow-up) of the primary outcome (e.g., depression scores) and all secondary outcomes will be analyzed using Analysis of Covariance (ANCOVA) for continuous outcomes that meet model assumptions. For outcomes that are not continuous or do not meet ANCOVA assumptions, appropriate generalized linear models will be used, specifying the distribution and link function according to the nature of the data (e.g., logistic regression for binary outcomes). The change score will be the dependent variable, with group (EG or CG), time points (e.g., post-intervention, follow-up), and their interaction included as fixed effects. Baseline values and relevant confounding variables (e.g., age, sex) will be included as covariates to adjust for initial differences and control for potential confounders. Model assumptions (e.g., normality, homogeneity of variances, linearity) will be assessed using diagnostic plots and statistical tests. In cases where assumptions are violated, data transformations or non-parametric alternatives will be considered. Effect sizes (with 95% confidence intervals) and statistical significance will be reported for the effects of group (between-subjects), time (within-subject), and the group × time interaction. Partial eta squared (ηp^2^) will be reported for ANCOVA, with effect sizes interpreted as small (ηp^2^ ≥ 0.01), medium (ηp^2^ ≥ 0.06), and large (ηp^2^ ≥ 0.14) according to Cohen’s guidelines [84,85]. Statistical significance will be set at *p* < 0.05. To address the issue of multiple comparisons, *p*-values will be adjusted using the Bonferroni correction [86]. The primary analysis will follow a per-protocol approach, including only participants who attended at least 80% of the intervention sessions. Missing data will be handled using an intention-to-treat (ITT) approach, ensuring that all randomized participants are included in the analysis. A dropout analysis will be conducted to determine whether participants who withdraw differ significantly from those who complete the study. Additionally, sensitivity analyses will be performed to confirm the robustness of the results under various assumptions about missing data. As high attrition is common in internet-based interventions for depression [39,40], these strategies are essential to reduce the risk of attrition bias and preserve internal validity [87]. All statistical analyses will be performed using STATA version 16.0 (StataCorp LP, College Station, TX, USA).

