### 2.3. Sample Size and Randomization

To detect a minimum mean difference of 8.26 in the primary outcome (depression symptoms), with an assumed standard deviation of 9.36, a sample size of 50 participants (25 per group) was calculated. These assumptions were based on the results of Stelzer et al. [38], who conducted an RCT involving individuals with depression undergoing a structured physical exercise psychotherapy intervention. Although their intervention modality was not delivered online, the target population and outcome measure were comparable to those used in the present study. The observed change in depressive symptoms in that trial was considered clinically meaningful and therefore appropriate to inform the sample size estimation in the context of exercise-based interventions for depression. This calculation assumed an alpha error of 0.05 and a statistical power of 85%. To accommodate potential loss to follow-up, 80 participants were initially recruited, accounting for a possible dropout rate. This ensures sufficient statistical power for the SONRIE study throughout its duration.

Participants were randomized in a 1:1 ratio to either the Experimental Group (EG; n = 40) or Control Group (CG; n = 40), ensuring balance in sex, age, and clinical severity of depression. The randomization process was conducted using a computer-generated sequence through STATA version 16.0 (Stata Corp, College Station, TX, USA). To prevent selection bias, allocation concealment was ensured by using a centralized randomization procedure, where the sequence was generated and stored by an independent researcher not involved in recruitment, intervention, or data collection. Group assignments were only revealed to participants after baseline assessments were completed, ensuring that neither researchers nor participants could predict or influence the allocation process.

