After randomization, four participants from the CG withdrew, leaving 36 participants in this group. Subsequently, the impact of the COVID-19 pandemic led to further attrition, reducing the CG to 25 by the post-intervention assessment and to 16 by the 8-week follow-up. In contrast, the EG showed better retention, with 37 participants remaining at the end of the study. Of these, 30 attended over 80% of the sessions. A flowchart detailing participant progression is presented in Figure 1. The higher dropout rate observed in the CG may be partially explained by reduced motivation in the absence of an active intervention. In addition, elevated attrition is a well-documented phenomenon in digital health trials, especially in the context of self-guided or internet-based interventions. As described in the “law of attrition” [39,40], such patterns are often expected and reflect typical user behavior rather than methodological flaws. Similar adherence challenges have been reported in previous web-based trials for depression and anxiety [39,40].

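### Section 2.8 promises that all randomised participants are analysed, but an ANCOVA of observed BDI change scores does not deliver this, and its handling of two visits per person is open to two readings with different samples and tests

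*Protocol article*

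**What the plan says.** Section 2.8 of the protocol article says that between-group differences in change "will be analyzed using Analysis of Covariance (ANCOVA) for continuous outcomes that meet model assumptions". The dependent variable is the change score at post-test and at 8-week follow-up, "with group (EG or CG), time points (e.g., post-intervention, follow-up), and their interaction included as fixed effects". Baseline values and confounders are covariates. Results are to be reported for "the effects of group (between-subjects), time (within-subject), and the group × time interaction". The assumptions to be checked are given as examples: "Model assumptions (e.g., normality, homogeneity of variances, linearity) will be assessed using diagnostic plots and statistical tests". Independence of observations is not among them.

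On missing data the same section says: "Missing data will be handled using an intention-to-treat (ITT) approach, ensuring that all randomized participants are included in the analysis". It also promises a dropout analysis and sensitivity analyses under different missing-data assumptions, without naming a method.

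Section 2.3 gives the losses. Four controls left after randomisation, with further attrition "reducing the CG to 25 by the post-intervention assessment and to 16 by the 8-week follow-up". The experimental group had 37 of 40 at the end of the study.

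**The concern.** Each participant can supply two change scores that share one baseline and one person. Section 2.8 names group, visit and their interaction but does not say how the two scores from one person are linked. Two analysts could follow the text, fit different models, and obtain different samples and p-values for the primary outcome.

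The statement on missing data is the firmer problem. Intention to treat defines an analysis set and is not a method for missing values. Someone with no BDI after baseline has no change score and cannot enter an ANCOVA of observed changes. By the end of the study 24 of 40 controls (60%) had been lost, against 3 of 40 (7.5%) in the experimental group. A promise that everyone is included therefore carries real weight here, and Section 3 relies on it as protection against attrition bias.

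**Working it through.** **The plan's own figure.** Section 2.3 states a difference of 8.26, SD 9.36, alpha 0.05 and power 85%, giving 25 per group. Two-sided, 2 × (1.960 + 1.036)² × (9.36/8.26)² = 23.1, so 24 per group by the normal formula. By the noncentral t, 24 per group gives 84.9% power and 25 gives 86.4%. The stated 25 is reproduced and does not bear on this point.

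**Inputs.** From Section 2.3: 40 + 40 randomised; controls 25 at post-test and 16 at follow-up; experimental group 37 at study end. Assumed:
- 37 in the experimental group at post-test as well (the text does not give this count)
- the 16 controls at follow-up are among the 25 at post-test
- two-sided 5% tests
- data missing completely at random in the simulations
- a residual correlation ρ of 0.3 to 0.7 between a person's two change scores, which the article does not give.

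**Reading A: classical repeated-measures ANCOVA, complete cases.**
- Analysed: 37 + 16 = 53 of 80 (66%), that is 37/40 = 93% of the experimental group and 16/40 = 40% of controls.
- Observed post-test scores discarded: 25 − 16 = 9 controls.
- Variance of the post-test contrast relative to using all observed post-test scores: (1/37 + 1/16)/(1/37 + 1/25) = 0.0895/0.0670 = 1.34. If all 40 in the experimental group were seen at post-test, it is 0.0895/(1/40 + 1/25) = 0.0895/0.0650 = 1.38.
- Simulated type I error (6,000 runs per setting): 4.5% to 5.5% for both the group and the interaction test.

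**Reading B: two rows per person treated as independent.**
- Analysed: 37 + 25 = 62 of 80 (78%), or 40 + 25 = 65 of 80 if nobody in the experimental group was missing at post-test.
- With balanced complete data, the variance of a person's two-visit mean is proportional to (1 + ρ)/2 but is taken as 1/2. The true size of the group test is 2[1 − Φ(1.96/√(1 + ρ))].
- The variance of the difference between visits is proportional to 2(1 − ρ) but is taken as 2. The true size of the interaction test is 2[1 − Φ(1.96/√(1 − ρ))].
- The simulations use a baseline covariate, 37/37 against 25/16, and 6,000 runs per setting:

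| ρ | Group, formula | Group, simulated | Interaction, formula | Interaction, simulated | Post-test contrast, simulated | Follow-up contrast, simulated |
|---|---|---|---|---|---|---|
| 0.3 | 8.6% | 8.8% | 1.9% | 2.4% | 5.3% | 4.9% |
| 0.5 | 11.0% | 9.9% | 0.6% | 0.8% | 5.1% | 4.3% |
| 0.7 | 13.3% | 12.7% | 0.03% | 0.3% | 5.4% | 5.0% |

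Repeat simulations differ by a few tenths of a point. Taken together they give about 8–13% for the group test and 0.2–2.6% for the interaction. The contrasts at a single visit are hardly affected, because nobody appears twice within a visit.

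**Under both readings.** No post-test change score exists for 40 − 25 = 15 controls, and no follow-up change score for 40 − 16 = 24. Neither model reaches 80 from observed change scores.

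**The case against.** A reader might infer that the planned model simply has the wrong error rate. The article does not support that. It says certain terms are fixed effects, not that nothing else is in the model, and it labels time as within-subject. That is repeated-measures language and fits poorly with independent rows. On that reading the size is near 5% when data are missing completely at random. Even with independent rows, only the visit-averaged effect is too liberal; the interaction is conservative and the per-visit contrasts are sound. The two faults are alternatives and do not add up.

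A reader might also infer that all 80 cannot be included. That is too absolute: imputation before the ANCOVA, or a suitable likelihood model, would include them. Complete-case deletion is stated nowhere, so the 34% is the consequence of one usual implementation. The covariance structure and the imputation method are details that an article may leave to a fuller plan.

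The counts used are also not those of the named primary analysis, since "The primary analysis will follow a per-protocol approach, including only participants who attended at least 80% of the intervention sessions", and Section 2.3 reports 30 experimental participants above that threshold. With 30, the visit-averaged test under independent rows is still at about 8–12%. The clash between a per-protocol primary analysis and intention to treat is a separate matter.

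What remains is not an omission. The article names a model and asserts a property of it, and that model applied to observed change scores does not have the property. Unnamed sensitivity analyses do not change the main model.

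**Conclusion.** The point stands in a limited form. Section 2.8 presents intention to treat as the means by which everyone randomised is analysed, and an ANCOVA of observed change scores does not achieve that. It reaches at most 53 of 80 as a classical repeated-measures ANCOVA, which is the reading the text favours, or at most 62 of 80 with independent rows. The first throws away observed post-test data from 9 controls and raises the variance of the post-test contrast by about 34%. The second distorts the averaged group test and the interaction in opposite directions.

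The head counts rest on 37 in the experimental group at post-test, which the flow diagram in Figure 1 should settle. The error rates rest on the assumed correlation and on data missing completely at random. With 60% of controls lost against 7.5% in the experimental group, that missingness assumption is hard to take for granted, so a size near 5% does not show that a complete-case comparison is unbiased.

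**What to change.** In Section 2.8, replace the ANCOVA for BDI with a likelihood-based mixed model for repeated measures. Use BDI at post-test and follow-up as outcomes; unstructured within-participant covariance; and fixed effects for group, visit, group × visit, baseline BDI and baseline BDI × visit. Alternatively use the constrained longitudinal version, with baseline in the outcome vector and a common baseline mean, so that all 80 contribute. Section 2.3 supports that constraint: "Group assignments were only revealed to participants after baseline assessments were completed". Read the difference between groups at each visit from the model.

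Replace the sentence on missing data with a statement that:
- the model assumes data missing at random
- participants with no BDI after baseline contribute only under the constrained version or after multiple imputation
- the sensitivity analyses already promised will cover departures from missing at random.

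Under the constrained version, people with baseline only still supply no post-baseline outcome. Their inclusion does not replace the sensitivity analyses.

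The cost is a rewritten paragraph and a few lines of code in the STATA version already named, with no new data or patients. Compared with independent rows, the interval for the visit-averaged effect becomes wider, by √(1 + ρ), or about 1.14 to 1.30 for balanced data with ρ from 0.3 to 0.7.

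### The 85% power assumes one unadjusted BDI test at 0.05, but the Bonferroni rule has no defined family and does not exempt the BDI, so that power is not secured

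*Protocol article*

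**What the plan says.** Section 2.3 of the protocol article gives the design figures: "To detect a minimum mean difference of 8.26 in the primary outcome (depression symptoms"), "with an assumed standard deviation of 9.36", from which "a sample size of 50 participants (25 per group) was calculated". On the error rates it says "This calculation assumed an alpha error of 0.05 and a statistical power of 85"%. It mentions no adjustment for multiple tests. Eighty participants were recruited, and the section explains the excess over 50 as cover for dropout.

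Section 2.8 treats the primary outcome "and all secondary outcomes will be analyzed using Analysis of Covariance (ANCOVA"). The model contains group, time point and their interaction, and significance is to be reported for all three. There are two post-baseline visits: post-intervention and the 8-week follow-up. The significance level is 0.05, and p-"values will be adjusted using the Bonferroni correction". The section does not list the tests in the Bonferroni family, give their number, or say whether the BDI belongs to it. No section names one visit or one model effect as the deciding BDI test, and the primary aim in section 1 covers both immediate and sustained effects.

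**The concern.** The sample size and the analysis use alpha differently for the outcome that decides the trial. Section 2.3 spends the whole 0.05 on one BDI test. The rule in section 2.8 is unrestricted, so taken literally it divides that 0.05 by some number m that the article does not give.

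Setting the secondary outcomes aside does not settle the matter. The BDI alone can supply two tests (two visits) or three (three model effects), because no single contrast is named.

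Two things are at stake. A true effect of the planned size could miss significance because of a divisor that the sample size never allowed for. And section 2.1 says that the study was completed in October 2020, so a family left open in writing could be settled with the results in view.

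**Working it through.** **Inputs.** Difference 8.26, SD 9.36, alpha 0.05, power 85% and 25 per group come from section 2.3. Retention comes from the same section: 25 controls at post-intervention, 37 experimental participants at the end of the study, 30 of them above 80% attendance. Sidedness is not stated. I take two-sided, because a one-sided normal approximation gives 19 per group and does not match.

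**Method.** Two-sample t-test with
- d = 8.26 / 9.36 = 0.882
- noncentrality = d / √(1/n₁ + 1/n₂)
- df = n₁ + n₂ − 2
- two-sided critical value at alpha = 0.05/m

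**Step 1: reproduce the stated size.** At 25 per group, noncentrality = 0.882 / √(2/25) = 3.12, df = 48 and the critical value is 2.011, so power is 86.4%. At 24 per group it is 84.9%. The smallest size reaching 85% is therefore 25 per group, as stated. The article's figure is right for one unadjusted two-sided test.

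**Step 2: put the BDI inside a family of m tests.** At 25 per group the critical value rises to 2.314 for m = 2 (alpha 0.025) and to 2.481 for m = 3 (alpha 0.0167).

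**Step 3: repeat at the group sizes reported.** The 30 v 25 set approximates the per-protocol set that section 2.8 makes primary: the 30 experimental participants above 80% attendance and the controls present at post-intervention. The 37 v 25 set assumes that the 37 retained at the end also give the post-intervention number.

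| Groups | Noncentrality | m = 1 | m = 2 | m = 3 |
|---|---|---|---|---|
| 25 v 25 (design) | 3.12 | 86.4% | 78.7% | 73.6% |
| 30 v 25 (approx. per-protocol) | 3.26 | 89.2% | 82.6% | 78.1% |
| 37 v 25 (post-intervention) | 3.41 | 91.8% | 86.3% | 82.5% |
| 40 v 40 (all randomized) | 3.95 | 97.4% | 95.0% | 93.1% |

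Unadjusted, every row meets 85%. In the first two rows a divisor of two is enough to go below it, so at post-intervention any shortfall there comes from the Bonferroni rule and not from attrition.

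**Step 4: allow for the baseline covariate.** These figures ignore it. If 9.36 is a raw-score SD and baseline correlates r with outcome, the residual SD is 9.36 × √(1 − r²). The article gives no r. Assuming r = 0.3 to 0.5, power at 30 v 25 with m = 2 is about 86% to 92% (noncentral t, df = 52). If 9.36 is already the SD of change, the gain may be smaller. The article does not say which it is.

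**The case against.** The strongest reply is that the BDI may not be inside the family at all. The article names one primary outcome, and a single primary test needs no correction against secondary outcomes. The Bonferroni sentence could refer to the secondary outcomes only, or to follow-up comparisons between time points. On either reading the deciding BDI test keeps 0.05 and the power stands. A reader might infer that the trial is certainly short of its stated power; the text does not support that, because it allows m = 1.

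A reader might also infer that the BDI is to be corrected against every fitness, blood and psychological measure, with power collapsing as a result. No sentence says so, and I attach no figure to that reading.

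Three further points stand. At 37 v 25 a divisor of two leaves 86.3%, and with all 80 analysed power holds to m = 10 (85.1%). Section 2.8 does include baseline as a covariate, which may recover power. And Bonferroni is conservative, so false positives are not the issue.

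Two replies do not carry. The surplus over 50 was recruited for dropout, not to pay for multiplicity. Nor is this only detail left to an analysis plan: the article states a rule without limits, and that rule, applied as written, conflicts with the alpha behind its own sample size.

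**Conclusion.** The concern holds as an unsecured power claim. Section 2.3 is arithmetically sound for one two-sided BDI test at 0.05; section 2.8 does not guarantee that the BDI will be tested that way.

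If it is adjusted for two or three tests, power falls from 86.4% to 78.7% or 73.6% at the design size, and from 89.2% to 82.6% or 78.1% in the approximate per-protocol set. At 37 v 25 the 85% survives two tests but not three (82.5%).

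These figures rest on a two-sided t-test without baseline adjustment, the planned difference and SD, and my approximation of the per-protocol set. With useful baseline adjustment the loss could be small or absent. This should be fixed, but it does not undermine the trial.

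**What to change.** In section 2.8:

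1. Name one BDI group contrast, at post-intervention, tested once at two-sided 0.05 outside any adjustment. This is the test that section 2.3 was sized for.
2. Test the 8-week BDI contrast at 0.05 only if the first is significant. This fixed sequence keeps the error rate over both BDI tests at 0.05.
3. Apply multiplicity control only to the listed secondary outcomes, using Holm in place of Bonferroni. Holm holds the same familywise error rate and rejects whatever Bonferroni rejects, and sometimes more.

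If the sponsor wants the BDI inside an adjusted family, state m and restate the power in section 2.3 at alpha 0.05/m.

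The change takes a few sentences and no further participants or data. It has two costs. The claim of a sustained effect, which is part of the primary aim, becomes conditional on the post-intervention result. And because the study was completed in October 2020, the change must be dated and declared as made after data collection.

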#### 2.6.1. Physical Domain

*Body composition*. A multifrequency bioimpedance analyzer (TANITA-MC780MA) was used to measure fat mass (kg), fat mass percentage, lean mass (kg), and lean mass percentage [44]. Participants were asked to urinate before the assessment, and fast for at least 2 h prior to the assessment. Body mass index was calculated as weight (kg) divided by height squared (m^2^). Waist and hip circumferences were measured in cm with an anthropometric tape (Lufkin W606PM, Washington, USA), following standardized guidelines [45].

*Blood pressure and heart rate.* Resting blood pressure and heart rate were assessed using an Omron M6 upper arm blood pressure monitor (Omron Health Care Europe B.V., Hoofddorp, The Netherlands). Measurements were taken twice, spaced two minutes apart, following a 5 min period of rest. Participants were seated with the non-dominant arm positioned at heart level, the cuff placed on the upper arm, and the palm facing upwards to ensure accuracy.

*Objective PA levels and sedentary time* were evaluated using a triaxial accelerometer (Actigraph GT3X, MTI, USA; ActiLife Software version 6.13.3) [46]. Participants wore the device for seven consecutive days on the waist at the center of the lower back, ensuring 24 h recording except during water-based activities. A valid day was defined as at least eight hours (480 min) of wear time, and data were considered valid if the participant recorded at least three valid days, including at least one weekend day [46]. Non-wear time was identified as 60 consecutive minutes of zero counts, with allowance for a 2 min interval of non-zero values, and validated using Troiano cutoff points [47]. Data were collected over 60 s epochs at a sampling rate of 30 Hz [46]. To ensure comparability with previous research, Freedson’s cutoff points were applied to classify PA intensities [48]. Additionally, daily step counts and sedentary bouts lasting ≥30 min were analyzed to provide a more detailed understanding of activity patterns. In addition, self-reported PA was collected through the Global PA Questionnaire (GPAQ), which has been validated [49] and adapted to the Spanish context [50].

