
*Blood biomarker analyses* were collected from each participant after an overnight fast (between 08:00 and 09:00 h) via venipuncture. The blood was drawn into K2-EDTA tubes and kept on ice until processing, which commenced within 10 min post-extraction to preserve sample integrity. Tubes were centrifuged at 1700× *g* for 15 min at 4 °C to separate plasma and serum. One milliliter (1 mL) of plasma was then aliquoted into cryotubes, and, for ES analyses specifically, 8 µL of orlistat (250 µg/mL in ethanol) were added to each aliquot to prevent analyte degradation. All samples were stored at –80 °C until further analysis. Where serum was required (e.g., BDNF measurements), blood was collected in serum-separator tubes and processed according to standard laboratory protocols. Biomarkers for the ES, neuroplasticity, and cardiovascular disease risk were measured. For the ES, plasma level concentrations of eCBs (AEA, 2-AG) and their analogs [oleoylethanolamide (OEA), linoleoyl glycerol (2-LG), oleoyl glycerol (2-OG), dihomo-γ-linolenoyl ethanolamide (DEA), docosahexaenoylethanolamide (DHEA), linoleoylethanolamide (LEA), and stearoylethanolamide (SEA)] were obtained following a previously validated method [63]. Briefly, 0.5 mL of thawed plasma was transferred to 12 mL glass tubes, spiked with deuterated internal standards (e.g., AEA-d4, DHEA-d4, LEA-d4, OEA-d4, 2-AG-d5, and 2-OG-d5), and extracted with tert-butyl methyl ether. After evaporation to dryness, the extract was reconstituted in 100 µL of water: acetonitrile (10:90, *v*/*v*) with 0.1% formic acid, then transferred to HPLC vials. Analyses were performed using liquid chromatography–tandem mass spectrometry (LC-MS/MS) [64,65] on a Waters Acquity UPLC system coupled to a Xevo TQ-S micro–Mass Spectrometer, with a BEH-C18 column (2.1 × 100 mm, 1.8 µm) at 55 °C and a flow rate of 0.4 mL/min. The mobile phase comprised 0.01% (*v*/*v*) formic acid in water (solvent A) and 0.01% (*v*/*v*) formic acid in acetonitrile (solvent B), and detection used multiple reaction monitoring (MRM). Quantification was achieved by isotope dilution, with quality control samples (injected across four batches) yielding RSDs of 7.0–10.7%. For the neuroplasticity assessment, BDNF was measure from serum using an indirect enzyme-linked immunosorbent assay (ELISA) utilizing a specific kit (RAyBio Human BDNF ELISA Kit, Chemicon, Temecula, CA, USA) designed for high sensitivity and specificity [66]. The assay was performed according to the manufacturer’s instructions, with each sample measured in duplicate, and results were expressed in ng/mL. Cardiovascular risk factors (total cholesterol, HDL-cholesterol, LDL-cholesterol, and triglycerides), glycemic control markers (glucose, insulin, glycated hemoglobin HbA1c, and insulin resistance assessed by HOMA-I), inflammatory markers (high-sensitivity C-reactive protein, tumor necrosis factor-alpha, and interleukin 6), and liver metabolism enzymes (alanine aminotransferase, aspartate aminotransferase, and alkaline phosphatase) were measured using standardized clinical protocols in accordance with the Andalusian Public Health System Biobank guidelines. Complete blood counts (hemoglobin, hematocrit, leukocytes, platelets), renal function (creatinine, urea), and electrolytes (sodium, potassium) were also measured using routine automated laboratory methods.

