**Secondary outcome**	
**Physical Domain**	
Body Composition	- Weight, fat mass (kg), fat-free mass (kg), and body fat (%) by TANITA MC-780MA Bioimpedance Analyzer - Height (cm) by a stadiometer - Waist and hip circumferences by an anthropometric tape
Blood Pressure and Heart Rate	- Omron M6 Monitor upper arm blood pressure monitor
Physical Activity and Sedentary Time	- ActiGraph GT3X Accelerometer - Global PA Questionnaire (GPAQ)
Health-Related Physical Fitness	- CRF by the 6-Minute Walk test and the 3-Minute Step test - Muscle strength by the Chair Stand, the Standing Long Jump, the Arm Curl, and the Handgrip strength tests - Flexibility by the Back Scratch and Chair Sit and Reach tests - Agility by the 8-Foot Up-and-Go test - Balance by the Unipedal Stance test - Gait speed using the 4 m and 6 m walk tests - Self-reported fitness by International Fitness Scale
Blood Biomarker Analyses	- Endocannabinoid levels (AEA; 2-AG; OEA; 2-LG; 2-OG; DEA; DHEA; LEA; SEA) - Lipid and glycemic profiles, inflammatory markers and liver enzymes - Brain-Derived Neurotrophic Factor (BDNF)

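### For the secondary outcomes, Holm should replace plain Bonferroni at the same error rate, and section 2.6 and Table 1 should give one outcome list; the power gained is modest

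*Protocol article*

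**What the plan says.** Section 2.8 states that the primary outcome "and all secondary outcomes will be analyzed using Analysis of Covariance (ANCOVA") where model assumptions hold, and by generalized linear models otherwise. "Statistical significance will be set at *p* < 0.05", and for multiple comparisons the p-values "will be adjusted using the Bonferroni correction". No family, divisor or adjusted level is given.

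The outcomes stand in two places, and section 2.4 refers to Table 1 for the tools used for all of them. Section 2.6.1 goes further than Table 1:

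- **Body composition:** the analyzer "was used to measure fat mass (kg), fat mass percentage, lean mass (kg), and lean mass percentage", and BMI is calculated. Table 1 has weight, fat mass, fat-free mass and body fat %, with neither lean % nor BMI.
- **Blood:** "Complete blood counts (hemoglobin, hematocrit, leukocytes, platelets), renal function (creatinine, urea), and electrolytes (sodium, potassium) were also measured". Apart from endocannabinoids and BDNF, the blood row of Table 1 has only "Lipid and glycemic profiles, inflammatory markers and liver enzymes".
- **Fitness:** the five-repetition chair stand and three static balance positions are in the text but not in Table 1.
- **Weight** is named as a measurement in Table 1 but not in the text.

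**The concern.** Two things look improvable. First, the article fixes a single-step correction although a uniformly better one exists at no cost in error control. Every rejection by Bonferroni is also a rejection by Holm, and Holm sometimes rejects more.

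Second, a Bonferroni or Holm threshold depends on how many tests are in the family. If the family is the listed secondary outcomes, the article offers two lists, so the threshold cannot be derived from it. Secondary objectives (i) and (ii), on physical health, biomarkers and psychological dimensions, rest on these tests.

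**Working it through.** **The plan's own figure.** Section 2.3 gives a difference of 8.26, SD 9.36, alpha 0.05 and power 85%. The standardised effect is d = 8.26/9.36 = 0.882. The two-sided noncentral t gives power 0.849 with 24 per group and 0.864 with 25, so the stated 25 per group is reproduced. That calculation is for the primary outcome at the unadjusted level.

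**Counting the listed outcomes** (one score per test or scale, per visit):

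| Domain | Section 2.6 |
|---|---|
| Body composition | 7 |
| Blood pressure, heart rate | 3 |
| Activity and sedentary time | 7 |
| Fitness | 17 |
| Blood | 32 |
| Psychological | 13 |
| **Total** | **79** |

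The items found only in the text are the five-repetition chair stand (1), static stances (3), BMI (1), lean % (1), blood counts (4), renal markers (2) and electrolytes (2), which make 14. Table 1 therefore gives 79 − 14 + 1 (weight) = 66. The count is a matter of reading: other readings of section 2.6 run from 75 to 105, the latter if subscales count separately.

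**Per-test level.** 0.05/79 = 0.00063 and 0.05/66 = 0.00076.

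**Power per outcome.** Section 2.3 reports 25 controls at post-test and 37 in the experimental group at the end of the study; I use 37 for post-test too. The noncentrality is d × √(37 × 25/62) = 0.882 × √14.92 = 3.41 on 60 df.

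| Tests in family | Critical t | Power |
|---|---|---|
| 1 (unadjusted) | 2.00 | 0.918 |
| 66 | 3.55 | 0.452 |
| 79 | 3.61 | 0.431 |

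At follow-up, with 37 v 16, power falls from 0.825 unadjusted to 0.263 with 79 tests. At d = 0.5 with 37 v 25 it is 0.057 with 79 tests.

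**Why Holm is valid.** Order the p-values and reject the i-th smallest while p(i) ≤ 0.05/(m − i + 1). Let m0 hypotheses be truly null. When the first true null is rejected, at most m − m0 rejections came before it, so its p-value is at most 0.05/m0. The chance that any of the m0 true nulls falls that low is at most m0 × 0.05/m0 = 0.05, whatever the correlations.

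**What Holm returns with 79 tests.** The threshold relaxes slowly: 0.05/79 = 0.00063 at first, 0.05/63 = 0.00079 after 16 rejections, and 0.05/39 = 0.00128 after 40. Simulation at d = 0.88, 37 v 25, correlation 0 or 0.5:

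| True effects of 79 | Gain in points |
|---|---|
| 4 | 0.1 to 0.2 |
| 16 | about 1 |
| 40 | about 3 |
| 79 | 9 to 12 |

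At d = 0.5 the gain is at most 0.9 points. Simulated family-wise error stayed at or below 0.05 for both methods.

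**Small families.** If the correction is meant only for a few contrasts, the gain is about 2 to 5 points for 3 to 6 tests. A check by simulation (d = 0.88, 37 v 25) gave about 3 points with two of three or three of six effects real. It gave almost nothing with one real effect, and 6 to 13 points if all were real.

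**Other levers.** Dropping about 5 redundant results (79 to 74) moves power from 0.431 to 0.439. A single-step method that uses the correlations gives 0.453, 0.497 and 0.563 at an assumed common correlation of 0.3, 0.5 and 0.7.

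**The case against.** The strongest objection is that the article never says Bonferroni runs over the whole outcome list. Correction over visits, or over contrasts within one model, fits the wording equally well, and the definition of the family may properly sit in an analysis plan not shown. This stands. The figure of 79 is therefore a conditional illustration, and the silence on the family is not itself a fault. It does not touch the case for Holm, which holds for any family.

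A second objection is that the fall from 92% to 43% is the price of adjusting for some 80 tests, not of choosing Bonferroni over a step-down method. This also stands. A reader might infer that a step-down procedure gives that power back; the calculations show that it does not.

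Three further inferences are tempting and fail:

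- Bonferroni does not assume independent tests, and testing far below 5% is what buys family-wise control.
- BMI does not duplicate weight within either list: the text has BMI without weight as an outcome, and Table 1 has weight without BMI.
- A larger rescue by Westfall-Young resampling rests on correlations and effect sizes that the article does not give.

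On the lists, it is fair to say that Table 1 names assessment tools and that the mismatch is editorial. Its effect on power is small (0.452 against 0.431). But both lists stand in one article, so condensation does not explain the difference.

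**Conclusion.** The point holds as a modest improvement on the secondary outcomes. Plain Bonferroni is valid but dominated by Holm at the same family-wise error rate under any dependence. If the family is the listed outcomes, the per-test level is about 0.0006 to 0.0008 and power about 43 to 45%, and Holm adds about 0 to 3 points unless nearly all effects are real. In a family of 3 to 6 tests it adds about 2 to 5 points. The mismatch between section 2.6 and Table 1 is real and should be settled.

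The power figures assume two-sided tests, the primary outcome's effect carried over to every secondary outcome, no gain from covariates, and equal correlations in the simulations. The article gives no secondary effect sizes or correlations. For effects near d = 0.5, Holm does not rescue a family of this size. Nothing here bears on the primary test.

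**What to change.** 1. In section 2.8, replace Bonferroni by Holm for the secondary outcomes. This changes one sentence and needs no new assumption. Date the change before the arm comparison, because the study was completed in October 2020 and a later switch to a less strict rule would look data-driven.
2. Make section 2.6 and Table 1 give one list before the arms are compared. The items to settle are the five-repetition chair stand, static balance, BMI, lean %, blood counts, renal markers and electrolytes (text only) and weight (Table 1 only). Since data collection is over, give a reason for any outcome removed, so that the edit is not read as selective reporting.
3. Optionally, use step-down Westfall-Young for the continuous ANCOVA outcomes. It needs a permutation run that respects the allocation balanced on sex, age and severity. It does not carry over directly to outcomes analysed by generalized linear models, and its extra gain cannot be predicted from the article.
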